### Intervention

To achieve the overall objective of the study, specific interventions focusing on agricultural training and nutrition education is implemented in *Treatment P* and *Treatment PC* for a period of 6 months. The components of these treatments are described in detail below.

#### Components of *Treatment P*

*Agricultural training on insect farming*. The agricultural training has been designed to teach intervention participants about small-scale insect farming. A training manual has been developed to ensure that the same information is transmitted to all participants. The training is based on behavior change techniques and key messages in relation to successful insect farming [42]. It covers a range of topics relevant to promoting insect farming for consumption. The topics are divided into six main elements, as shown in Table 2. Extensive training is provided in all villages where the *Treatment P* is implemented. The 15 participating household heads per village are divided into two groups during training sessions to ensure effective information dissemination to each participant and smooth feedback discussions. The training is conducted within one day and is organized into several sessions, scheduled to follow the main elements outlined in Table 2.

**Table 2 pone.0288870.t002:** Main elements of the agricultural training intervention.

Overall topic	Specific information
**1. Introduction**	• Welcome • Elements of the training sessions • Time schedule
**2. Overview of insects as nutritious and healthy food**	• Insects as food for human consumption • Benefits of insect farming
**3. Ecology and Biology of insects**	• Insect life cycle • Sex determination in insects • Insect behavior
**4. Starting an insect farm**	• Rearing house and site selection • Rearing equipment • Rearing container • Cage arrangement
**5. Management of an insect farm**	• Insect feeding and watering • Knowing signs and timing of egg laying • Preparing egg-laying substrate • Egg collection, incubation and hatching • Caring for pinhead • Hygiene maintenance • Pest and disease control
**6. Harvesting and post-harvest handling**	• Harvesting methods • Storage and transportation of insects • Post-harvest insect processing methods

The training activities begin with inviting the selected household heads to an information meeting. Here, participants are briefed on the purpose and nature of the intervention, what they can expect during the intervention, and what they are expected to do as participants. At this point, participants are made formally part of the intervention and assigned an identification number. Implementation teams are formed and receive training before commencing the interventions. They are responsible for providing the agricultural training according to the training manual. An implementation team consists of two persons assigned to half of the villages in each treatment arm and conducts the training on a rotating basis to avoid bias induced by the implementation team.

For example, if *Implementation Team 1* covers the first half of the villages in *Treatment P*, *Implementation Team 2* covers the first half in *Treatment PC*. Then, the team rotates, where *Implementation Team 1* covers the other half of the villages in *Treatment PC* while *Implementation Team 2* covers the other half in *Treatment P*. The training is given in a rolling sequence, i.e., the implementation team conducts training in one village at a time and continues until all villages are covered. The same implementation team visits each participant at least once a month to reinforce training messages and provide technical support for insect farming activities. These visits are important for participants as they give opportunities to raise questions and for the implementation team to tailor messages according to the specific contexts of the participant [43].

*Distribution of production starter kits for insect farming*. After the agricultural training, each participating household head receives a starter kit for free for small-scale insect farming. While the specific composition differs across the three countries due to differences in the types of insects selected for farming, the starter kits generally consist of live insects or eggs, insect rearing equipment and container, feed for insects, and a cleaning kit (see Table 3).

**Table 3 pone.0288870.t003:** Starter kits by country and insect species.

Country	Type of insect to be farmed	Main components of starter kits
**Ghana**	Palm weevil larvae (*Rhynchophorus phoenicis*)	• Adult larvae • Rearing container • Rearing equipment including rubber band, round bins, scale, stacker, shelves, aluminium mesh and rope • Start-up feeding substrate and a cleaning kit
**Kenya**	Crickets (*Scapsipedus icipe*, *Acheta domesticus)*	• A batch of eggs for hatching • Buckets • Cricket rearing equipment including cotton wool, spray bottle, egg hideouts, oviposition saucers, thermometer, and ant repellant • Starter feed and water dispenser, and a cleaning kit
**Uganda**	African edible bush crickets (*Ruspolia differens Serville*)	• Parent stock • Rearing cages • Rearing equipment, including egg-laying medium and egg hatching containers • Feed and water dispenser, and a cleaning kit

Each starter kit is expected to support 2–5 insect production cycles per participant with each cycle yielding 3–5kg of insects. The estimated cost of the starter kits is between 50–60 USD, 100–120 USD, and 10–15 USD per starter kit in Kenya, Uganda and Ghana, respectively.

The starter kits are distributed to participants on a rolling basis in each village immediately after the agricultural training and nutrition education sessions are completed. The kits are delivered directly to each household to ensure the participants receive them on time and get individualized advice on how and where to set up insect production on their land. The type, quantity and quality of starter kits are harmonized across participants to avoid a situation where the nature of the starter kits influences the impact of the intervention.

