### Analysis plan

We focus on the intent-to-treat (ITT) effects. Some participants may not attend to the agricultural training or nutrition education sessions despite being invited to the sessions. In the ITT analysis, we estimate the effects of the interventions by including all participants irrespective of whether they participated in the interventions or not. Our basic regression framework to estimate the ITT effect is:

$$Y_{i}=\beta_{0}+\beta_{1}T_{1}+\beta_{2}T_{2}+\varepsilon_{i}$$
(1)

*Y_i_* is the outcome variable for individual *i*, *T*_1_ and *T*_2_ are dummy variables which take the value 1 depending on which intervention the household in a village was assigned, 0 otherwise. The random error term is represented by *ε_i_*. The impacts of the interventions are given by *β*_1_ and *β*_2_. Standard errors are clustered at the village level to account for within village correlations. We conduct further analyses by extending Eq (1) to account for vectors of individual characteristics and other control variables, baseline and endline data, and treatment heterogeneity in terms of differences in the effects of the two interventions–*Treatment P* and *Treatment PC*. We assess any spillover effects by interviewing households who did not participate in the intervention. This assists in understanding whether and how the information regarding insect farming and consumption spread beyond the targeted households in the intervention [37].

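### The team rotation cancels constant team and order effects from PC minus P, but a team difference that changes between halves is aliased with that contrast, and Eq (1) omits team and half, which inflates its standard error if teams or halves differ

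*Protocol article*

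**What the plan says.** Under Components of Treatment P, the staffing rule is: "An implementation team consists of two persons assigned to half of the villages in each treatment arm". The stated aim is that each team "conducts the training on a rotating basis to avoid bias induced by the implementation team". One schedule is then given as an example. Team 1 covers the first half of the P villages while Team 2 covers the first half of the PC villages; they then exchange arms for the remaining halves. Delivery is sequential: "the implementation team conducts training in one village at a time and continues until all villages are covered". Contact continues after the training day: "The same implementation team visits each participant at least once a month to reinforce training messages".

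Under Analysis plan, Eq (1) regresses the outcome on T1 and T2 only, which "are dummy variables which take the value 1 depending on which intervention the household in a village was assigned, 0 otherwise". On variance: "Standard errors are clustered at the village level to account for within village correlations". The section then says that Eq (1) will be extended with individual characteristics, other control variables that are not named, and the difference between P and PC. Team and training order are neither named nor excluded.

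Under Intervention monitoring plan, the activity records list attendance, when sessions took place and on what topics, session length, kit delivery dates and visit dates. Team identity is not in that list. Under Trial status, recruitment is complete, the intervention is under way and follow-up data collection has not begun.

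**The concern.** PC versus P is the only contrast that isolates nutrition education. With two teams and a single swap, each team meets the arms in opposite order: in the example, Team 1 trains all its P villages before any PC village, and Team 2 does the reverse. Suppose one two-person team improves, tires or changes staff more than the other between halves. The villages then differ by arm for a reason unrelated to the curriculum, and no analysis of these data can tell the two apart. The article describes the rotation as avoiding team bias without this qualification.

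The second issue is precision. A design that balances a factor earns a smaller standard error only if the model contains that factor. Eq (1) does not contain team or half, so any difference between teams or halves goes into the residual village variation and widens the PC-versus-P interval.

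**Working it through.** **Inputs from the protocol article.** Effect size 0.25 (used as a standardized effect), ICC 0.06, 15 participants per village, significance level 0.05 (taken as two-sided), 64 villages for a two-group comparison, 33 villages per arm, and pilot adoption rates of 12% (Kenya) and 48% (Ghana). **Assumed, because the documents give no figures:** the size of any team, half or team-by-half effect.

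**1. The plan's own figure.** Variance of a village mean = 0.06 + 0.94/15 = 0.1227 SD². With 64 villages the variance of the difference is 4 × 0.1227/64. A noncentral t on 62 degrees of freedom gives 80.3% power, so the stated 80% reproduces. With 66 villages (33 per arm) the standard error is √(2 × 0.1227/33) = 0.086 SD and power is 81.5%.

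**2. Layout.** Code P/PC, first/second half and Team 1/Team 2 each as −1/+1.

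| Arm | Half | Team | Half × Team |
|---|---|---|---|
| P (−1) | −1 | −1 | +1 |
| P (−1) | +1 | +1 | +1 |
| PC (+1) | −1 | +1 | −1 |
| PC (+1) | +1 | −1 | −1 |

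Arm = −(Half × Team) in every row. Four of the eight possible combinations occur. With intercept, arm, team and half, the design matrix has rank 4. Adding the team-by-half term leaves it at 4, so that interaction cannot be separated from PC minus P.

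**3. What cancels.** Each team and each half appears in both arms. Since 33 is odd, a half is 16 or 17 villages. With a 16/16 or 17/17 split of first halves, 1/33 (3%) of a team difference remains in PC minus P. With 17/16, none of it remains, but 1/33 of a half difference does. A team difference of 0.25 SD thus leaves at most 0.25/33 = 0.008 SD. Had each team served one arm only, the whole 0.25 SD would have entered.

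**4. What does not cancel.** Let γ be the change in the team difference from the first half to the second. Bias in PC minus P is γ/2. A 0.25 SD effect is 0.25 × √(0.48 × 0.52) = 12.5 points at 48% adoption and 0.25 × √(0.12 × 0.88) = 8.1 points at 12%.

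| Assumed γ | Bias | Share of 12.5 points | Share of 8.1 points |
|---|---|---|---|
| 5 points | 2.5 points | 20% | 31% |
| 10 points | 5 points | 40% | 62% |

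With a standard error of 0.086 SD and no true effect, a 5-point bias (0.10 SD at 48%, 0.154 SD at 12%) raises rejection in one country from 5% to about 21% and 42% respectively. In simulation of village means (6,000 data sets), γ = 0.25 SD gave about 29% rejection with team and half in the model and without them: adjustment does not help here.

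**5. Precision.** A team gap d contributes between-village variance (d/2)²/[p(1−p)]. At p = 0.48:

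- d = 8 points: 0.0016/0.2496 = 0.0064
- d = 16 points: 0.0064/0.2496 = 0.0256

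If this variance is part of the 0.06 ICC, adding team multiplies the standard error by √[(0.1227 − 0.0064)/0.1227] = 0.974 or √[(0.1227 − 0.0256)/0.1227] = 0.889. That is a cut of 3% to 11%, and power at 0.25 SD rises from 0.81 to 0.83-0.89. If it comes on top of the ICC, the factors are √[0.1227/(0.1227 + 0.0064)] = 0.975 and √[0.1227/(0.1227 + 0.0256)] = 0.909, a cut of 3% to 9%.

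Simulation with team and half effects added on top of the ICC:

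| Team / half effect (SD) | Mean SE, Eq (1) | Mean SE, team and half added | Null rejection, Eq (1) | Power, Eq (1) → adjusted |
|---|---|---|---|---|
| 0.25 / 0.25 | 0.096 | 0.086 | 2.8% | 77% → 81% |
| 0.5 / 0.25 | 0.111 | 0.086 | 1.4% | 70% → 82% |

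The true spread of the estimate stays near 0.086 throughout, so the unadjusted test is conservative. These calculations use a continuous standardized outcome to match the 0.25; the primary outcomes are binary.

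**The case against.** - **The rotation does most of what it is meant to do.** A reader might infer that it fails to remove team bias. The documents do not support that: constant team differences and constant order effects both cancel to within 1/33. Nor does the article claim any gain in precision, so the omission of team from Eq (1) is a missed improvement and contradicts nothing.
- **Eq (1) is only the basic model.** The extension allows other control variables, and a statistical analysis plan may name team and order. The point is therefore about Eq (1) as written. One cannot conclude that the final analysis will ignore team.
- **The swap is an example.** It may differ by country. It is, however, the only schedule offered in support of the stated aim, and the aliasing is exact for it.
- **Drift may be small.** Both components have manuals, teams are trained beforehand, and monthly visits to P and PC villages may overlap in time once later villages are trained. This limits the interaction but does not exclude it.
- **The sizes are assumed.** No document gives a team gap or a drift. The upper precision figure within the ICC asks team alone to explain 0.0256/0.06 = 43% of the between-village variance, which is a lot. Omitting team costs power but does not invalidate the test.
- **Reach.** The article names the effects against control as its impacts and lists the P-versus-PC difference among further analyses. The full aliasing concerns that difference.

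These points narrow the concern and lower its weight. They do not affect the algebra, or the case for adding two covariates before endline.

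**Conclusion.** The point holds in a limited form. For the schedule illustrated, PC minus P is protected against constant team and constant order effects, but is inseparable from a change in the team difference between halves. The bias is half that change: 5 points for an assumed 10-point change, which is 40% of the target difference at 48% adoption and 62% at 12%. No covariate can remove it.

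Separately, Eq (1) as written gives too large a standard error for PC versus P if teams or halves differ. For assumed team gaps of 8 to 16 points at 48% adoption, the avoidable excess corresponds to a cut of about 3-11% (team variance within the ICC) or 3-9% (added to it). If neither teams nor halves differ, there is nothing to gain and almost nothing to lose. All these sizes rest on assumed team effects and on the example schedule being the one used.

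**What to change.** 1. Before endline data are collected, pre-specify team and half (or training order) as main effects in the PC-versus-P model. When control villages are in the same model, centre both terms among treated villages and set them to zero for control, so that β1 and β2 refer to the average team and half.
2. Take order from the dated activity records. Take team from the assignment schedule and keep it with those records, since team identity is not among the items listed.
3. In Components of Treatment P, state that the rotation protects against constant team and order effects only. Report a team difference that changes over time as a limitation of PC versus P; the covariates in step 1 improve the standard error and do not address this bias.
4. Where training has not yet been delivered, interleave P and PC villages within each team. With the intervention already under way, this may apply to few villages or none.

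Cost: two covariates (two degrees of freedom out of 64 for the two-arm comparison of village means), one revised sentence, one limitation, and a team identifier kept with the activity records.

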#### Components of *Treatment PC*

*Additional nutrition education component*. In addition to the intervention components in *Treatment P*, the *Treatment PC* includes the nutrition education designed to provide participants with specific nutrition knowledge about insects as food. This is expected to address the lack of information about the benefits of consuming insects, which in turn is expected to increase demand. Research suggests that demand creation is required for achieving high adoption rates of new food varieties [e.g. 37]. Nutrition education goes beyond only explaining the nutritional benefits of insects. It also addresses the lack of insect food preparation skills by providing demonstrations of how to prepare insect-based food. Specifically, households participate in live sessions involving cooking demonstrations and consumption of insect-based foods along with the provision of nutritional information. A manual for the nutrition education sessions is developed so that all participants receive identical information. The manual covers the topics shown in Table 4. Insects are expected to be consumed as whole cooked insects or they can be processed and blended with other conventional foods [44]. Thus, the cooking and consumption demonstration is based on porridge blended with insect flour, and whole cooked insects. The nutrition education component is implemented in villages assigned to *Treatment PC*. It is conducted within one day, comprising several sessions that cover the topics in Table 4. Households participating in the agricultural training are invited to attend the nutrition education training. As our focus is on households with children below five years of age, primary caregivers are specifically invited to participate, especially in cases where the head of the household is not the primary caregiver of the children. Similar to the agricultural training, implementation teams are formed and receive training to provide the nutrition education on a rotating basis. The implementation teams also provide refresher education when visiting participants in their households whenever necessary.

**Table 4 pone.0288870.t004:** Main elements of the nutrition education intervention.

Overall topic	Specific information
**1. Introduction session**	• Welcome • Time schedule • Elements of the training sessions • Aim and objective of training • Nutrition as a right • Importance of good nutrition to individuals, household and community
**2. Causes and consequences of nutritional deficiencies**	• Causes of poor nutrition • Consequence of poor nutrition • Effect of malnutrition to individuals • Preventive measures of malnutrition • Food groups and nutrition • Function of each food group • Breastfeeding • Contribution of animal source food to diet • How much to it (My plate)
**3. Nutritional benefits of insects**	• Nutritional benefits of insect consumption • Nutritional content of insects • Nutritional benefits of insects for child development • Food safety issues related to insects as human foods
**4. Insect cooking demonstration and consumption**	• Food processing • Insect food recipes • Cooking steps • Food tasting

#### Intervention monitoring plan

In line with previous protocols for RCTs [e.g. 43], we follow an intervention monitoring plan to record intervention activities and monitor outputs.

*Intervention activity records*. The intervention activity record involves tracking intervention activities. These include a) attendance of each participating household at agricultural training and nutrition education sessions; b) when and what topics were included in the sessions; c) length of each session; d) when production starter kits were delivered to each participant; and e) when implementation staff visits each participating household.

*Output monitoring*. Output monitoring involves a routine assessment of intervention outcomes during implementation [43]. The implementation team visits households participating in the interventions and conduct monitoring interviews and dialogue in each village.

### Outcomes

#### Overview of outcome variables and measurements

*Primary outcomes variables*. The primary outcome variables indicating the impacts of the interventions are: 1) whether farmed insects are consumed in the household, and 2) adoption of insect farming. The first primary outcome variable is measured during the baseline and endline surveys using questionnaires that inquire whether the participants cook and consume farmed insects. For participants, who cook and consume the farmed insects, they are asked to indicate the frequency of consumption within the last one year using a five-point scale ranging from 1–3 times per month to 1 or more times per day. The second outcome variable is measured through direct observation to determine whether the participant is still engaged in insect farming at the time the endline survey is conducted. Engaging in insect farming activities entails management of an insect farm, as well as harvesting and postharvest practices, as described in Table 2.

*Secondary outcome variables*. The secondary outcome variables are: 1) Insect farming and nutrition knowledge: is measured based on simple exam-like questions relating to the content of the agricultural training and nutrition education. In the questions addressing the agricultural training, participants are asked about their knowledge regarding starting an insect farm, managing an insect farm, and harvesting insects, as well as postharvest handling practices. In the questions addressing the nutrition education, participants are asked about their awareness of the nutritional content of insects and their importance for human consumption, as well as the insect-based food products that can be prepared and consumed by humans. This way of measuring knowledge enables us to effectively capture respondents’ ability to retain knowledge and memorize specific aspects of the agricultural training and nutrition education as a result of efforts made during and after the training. Our measurement of knowledge aligns with the suggestion by Kondylis, Mueller [45], and the existing literature on the adoption of climate-smart agricultural technologies in Africa [e.g. 37, 46, 47]; 2) Dietary diversity: is measured through child dietary diversity and household dietary diversity scores [48, 49]. Both scores are based on six food groups, including meat products, eggs, vegetables and fruits, starchy foods, dairy products, and pulses, legumes and nuts. Participants are asked to report whether and how often their children have consumed foods from each food group in the past seven days for the child dietary diversity score, and in the past thirty days for the household dietary diversity score; 3) Food insecurity perception: is measured based on the food insecurity experience scale presented in Cafiero, Viviani [50]; and 4) Perceived benefits and attitudes: is measured based on different questions focusing on peoples’ willingness to take risks in general, their risk attitude towards insects farming, and their willingness to adopt insect farming as an agricultural practice. The questions are developed based on relevant literature [e.g. 51–53]. Willingness to take risks is specifically measured using a ten-point scale from 0 (unwilling to take risks) to 10 (fully prepared to take risks) [51]. The risk attitude towards insect farming and willingness to adopt insect farming are measured using a five-point scale, ranging from strongly disagree to strongly agree. Information on all the aforementioned secondary outcomes are collected during both baseline and endline surveys.

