### Study design

The study involves a 1:1 cluster-RCT with two intervention arms. The first intervention arm focuses on insect production. It includes agricultural training on insect farming and the provision of insect production starter kits *(Treatment P)*. The second intervention arm is focused on insect production plus insect-based food consumption. It has the same intervention components as *Treatment P* plus an additional component focused on nutrition education and insect cooking demonstrations *(Treatment PC)*. A control arm with no interventions *(Control)* serves as a comparison group for the treatments. The effectiveness of the interventions is evaluated by comparing baseline and endline data collected one year apart.

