Study arm	Clusters	Baseline survey	Intervention with participant endline survey			Community endline survey
	Villages	Participants^a^ per village	Participants per village	Participants per arm	Participants per arm (extra 10% added)^b^	Participants per village^c^
Treatment *P*	33	30	15	495	545	15
Treatment *PC*	33	30	15	495	545	15
Control	33	30	0	0	0	30

Note: ^a^ Participants are household represented by the head of the household.

^b^ The number of participants per treatment arm was increased by 10% to account for attrition.

^c^ The remaining 15 participants per village from the baseline survey who are not part of the intervention are included in the community endline survey. No interventions are implemented in the control villages, therefore, all the 30 household are included in this survey.

To ensure research integrity and methodological rigor, the village randomization process is blinded to all individuals involved in the research and households residing in the 99 villages prior to the intervention. A randomized sequence is generated in STATA [41] by a colleague not involved in the research. The outcome of the randomization is only revealed to project staff and households after the randomization process is completed. During the intervention, blinding is not maintained, except in the control villages where households are unaware of the intervention. Project staff members only visit control villages during the baseline and endline surveys, and no visits are conducted during the intervention to prevent information leakage and reduce potential biases that could arise from knowledge of the intervention in the control group.

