Our focus on educational programs to promote the production and consumption of insects in Africa aligns with suggestions in the literature regarding strategies for promoting insects as a food source. As discussed in Maya, Sterling [59], education can play a key role in increasing the supply of sustainable foods through insect production, particularly in regions where insects are already considered a traditional food [5]. Additionally, this strategy can be applied in areas, notably Western countries, where insects are often associated with disgust. In such countries, education can help mitigate the perception of disgust and enhance willingness-to-eat insects by increasing interest in insects as food and fostering positive experiences regarding the idea of consuming insects [59, 60]. In addition to education, social influence can play a significant role in promoting insects as food, as indicated by review studies [61–63]. Social influence is also utilized as a strategy to increase the adoption of climate-smart agricultural practices in developing countries [35, 64]. Our study design enables us to investigate whether this factor plays a role in promoting insect farming and consumption. We ask baseline survey participants, who were not selected for the intervention, about their awareness and sources of information regarding insect farming and consumption. We also examine how this awareness influences their attitude and perception of insects as food, their willingness to adopt insect farming, and whether they have established an insect farm or consumed farmed insects.

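### The consumption item does not exclude food from the PC-only cooking sessions and has no below-monthly category; how adoption is confirmed outside intervention households is unclear

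*Protocol article*

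**What the plan says.** **Consumption.** The protocol's Outcomes section names the primary outcomes as "1) whether farmed insects are consumed in the household, and 2) adoption of insect farming". The first is measured at baseline and endline "using questionnaires that inquire whether the participants cook and consume farmed insects". Those who do are then asked how often, "within the last one year using a five-point scale ranging from 1–3 times per month to 1 or more times per day". Effects are evaluated by "comparing baseline and endline data collected one year apart" (Study design), with the six-month intervention in between.

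In the PC arm only, "households participate in live sessions involving cooking demonstrations and consumption of insect-based foods" (Components of Treatment PC; food tasting is listed in Table 4). The starter-kit text under Components of Treatment P says that kits are handed out once the agricultural and nutrition sessions in a village are finished.

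**Adoption.** The second primary outcome is "measured through direct observation to determine whether the participant is still engaged in insect farming" at endline. No intervention takes place in control villages, so "all the 30 household are included in this survey" (Table 1, note c), meaning the community endline survey. The non-selected households of the intervention villages are in the same survey (Data collection). For non-selected households, the Discussion says that the study examines "whether they have established an insect farm or consumed farmed insects", without naming a method.

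**The concern.** Three features of the two primary outcomes are not pinned down.

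1. **Session food.** PC households eat insects at a project event inside the recall year; P and control households do not. The kits come after the sessions, so this food cannot come from the household's own farm. If some PC households count it, part of the intervention is scored as its effect. The error would favour PC over control and PC over P, and the second of these contrasts is what shows the added value of nutrition education.
2. **Scale floor.** The lowest frequency on offer is 1–3 times per month over a year. A household that ate farmed insects only a few times is a true consumer with no matching answer. It must overstate its frequency, skip the item or change its yes to a no.
3. **Adoption.** The wording on observation (still engaged in farming) fits households that were given a kit. Controls are surveyed through the other endline component, for which no observation is mentioned. If one group is observed and the other only asked, the comparison mixes two methods.

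**Working it through.** **The plan's own figure.** Inputs from Sample size: effect size 0.25 (taken as standardized), power 0.80, significance level 0.05 (taken as two-sided), intra-cluster correlation 0.06, 15 per village.

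- Individually randomized: 2 × (1.96 + 0.8416)² / 0.25² = 251.2, so 252 per arm.
- Design effect: 1 + (15 − 1) × 0.06 = 1.84.
- Villages per arm: 252 × 1.84 / 15 = 30.9, so 31, or 62 in total.
- With a noncentral t distribution on J − 2 degrees of freedom, power is 0.790 at J = 62 villages and 0.803 at J = 64. The stated 64 is reproduced.

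With the planned 33 villages of 15, the effective size is 495 / 1.84 = 269 per arm.

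**Session food.** Let p be the true consumption rate, equal in P and PC, and f the share of PC non-consumers who answer yes only because of the session. The false PC–P difference is f × (1 − p). The documents give no value for f, so a range is shown. The values of p are the two pilot adoption rates in Sample size (12% and 48%) and an assumed 25% between them. The last figure in each cell is the chance that a two-sided 5% test wrongly declares PC above P (normal approximation, 269 per arm); without misreporting it is 2.5%.

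| True rate p | f = 2% | f = 5% | f = 10% |
|---|---|---|---|
| 12% | 0.02 × 0.88 = 1.8 points; 9% | 4.4 points; 31% | 8.8 points; 79% |
| 25% | 0.02 × 0.75 = 1.5 points; 6% | 3.7 points; 16% | 7.5 points; 49% |
| 48% | 0.02 × 0.52 = 1.0 point; 4% | 2.6 points; 9% | 5.2 points; 23% |

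At 2% the effect is small. At 10% it is material unless true consumption is high.

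**Scale floor.** One to three times per month over 12 months is 12 to 36 occasions. A household that ate once after each of the 2–5 cycles a kit supports has 2 to 5 occasions in the year, below the lowest category. So does one that ate monthly for, say, the last six months (6 occasions), because part of the recall year precedes kit delivery.

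**Adoption.** The relevant places, side by side:

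- Outcomes: direct observation of the participant.
- Data collection and Table 1: the participant endline survey covers intervention households; controls and non-selected households are in the community survey.
- Discussion: non-selected households are asked about awareness and information sources. Whether they have set up a farm is examined, by a method not named.

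No place says that controls are observed, and none says that they are not. If controls were only asked and a share g wrongly reported a farm, while treated households were observed without error, a true difference of 25 points would appear as 23, 20 or 15 points at g = 2%, 5% or 10%. The values of g are assumptions. The error would dilute the effect, not inflate it.

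**The case against.** A reader might infer that the primary outcomes are ascertained differently by arm. The documents do not support this for consumption. One item is described, and Table 5 gives the endline survey population as treatment and control groups. At most, one arm may misread a common question.

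A reader might also take the one-year recall as part of the yes/no outcome. It belongs to the frequency follow-up; the yes/no item has no stated window. That does not exclude session food either.

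The mechanism may be weak. The words for cooking, for farmed insects and for consumption in the household may already lead respondents to leave out a one-day demonstration, and a single tasting is itself below the lowest frequency category. This stands, and it is why bias is possible and not shown.

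The number of production cycles does not limit how often insects are eaten. A kit yields 2 × 3 = 6 to 5 × 5 = 25 kg, and training covers storage and processing. This also stands: the scale gap concerns households that in fact ate rarely, not all households.

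For adoption, it is tempting to say that controls only self-report. That is an inference. Table 1 calls control households participants too, so the observation rule can be read as covering every enrolled household. Control adoption should also be low, since controls receive no kits and eligible villages had no earlier exposure.

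Finally, the endline questionnaire is still to be redesigned and is not shown, so exact wording may be settled there. But the frequency range and the definitions of the primary outcomes are fixed in the protocol, and the redesign is meant to capture consumption experiences during the intervention fully. That makes an explicit exclusion more useful.

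**Conclusion.** The concern holds in limited form. Session food is not excluded from the consumption item, the recall year of the follow-up contains the PC-only sessions, and any error would favour PC. The size is unknown: 1.5–7.5 points at a true rate of 25%, and 1.8–8.8 points at 12%, if 2–10% of PC non-consumers counted session food. These figures rest on assumed misreporting and on equal true rates in P and PC; they are not estimates of actual bias.

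The missing below-monthly category is a defect of the stated scale and needs no such assumption. It affects the frequency item directly, and the yes/no outcome only if respondents change that answer. For adoption, the finding is lack of clarity, not demonstrated mixing of observed and self-reported data.

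**What to change.** Follow-up data collection has not begun (Trial status), so all of this can be done before endline:

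- Word the consumption item as farmed insects cooked and eaten at home, explicitly excluding food served at project sessions. Use the same wording in every arm and in both endline surveys.
- Add a category for less than once a month, and tie frequency to the period since first harvest. State a default window for households that had no harvest.
- State that adoption is confirmed by the same method in all arms, at least by direct observation wherever a surveyed household reports a farm. Reconcile the Outcomes section with the Discussion accordingly.

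Cost: questionnaire wording, and a few minutes at visits already planned. Observing only where a farm is reported avoids inspecting all 33 × 30 = 990 control and 2 × 33 × 15 = 990 non-selected households per country. Endline wording will differ slightly from baseline. This should matter little, because villages with earlier insect farming were not eligible and baseline consumption of farmed insects should be near zero.
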